### The intervention

The primary intervention will be at the hospital level and outcomes will be measured at the patient level. The intervention will consist of the following:The implementation of a formalised TTS form (Additional file 1: Appendix A)*,* used in two previous studies [15,16]). This form prompts documentation for relevant features of history (such as mechanism of injury) and physical examination of relevant body regions. Furthermore, the form prompts for review and documentation of relevant pathology and imaging results. The final part of the form includes a (new) injury list.All medical and nursing staff on trauma admitting wards will attend two education sessions on the rationale and use of the TTS form, provided by a chief or associate researcher in small-group work-shop format.Key stake holder engagement (Hospital executives, Directors of trauma admitting units; Emergency Department, General Surgery, Orthopaedic Surgery, Neurosurgery, Intensive Care Unit) with a clear directive to all levels of medical and nursing staff for compliance with training and education sessions and mandatory TTS form completion as part of routine care within 24 hours of admission.

Standard (existing) care will be at the discretion of the trauma admitting teams of the control hospitals. Standard care is defined as performing a clinical examination based on clinical judgment and without standardised forms. Data collection forms and procedures will be identical for both study arms. A TTS in the intervention phases is defined as completion of the formal TTS form within 24 hours of admission, where during standard care it is defined as a documented tertiary survey as part of a clinical examination within 24 hours of admission. A review of the previously known injuries only is NOT a tertiary survey.

Based on our own descriptive data [15,16], routine TTS are performed in approximately 25% of admitted multi-trauma patients. To truly assess the effect of a formalised TTS on missed injuries, the compliance in the intervention hospitals is aimed to be >90%, but will need to be at least 75% to be deemed an effective implementation of the intervention.

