### Randomisation

Participating hospitals (clusters) will be 1:1 randomised to either immediate (Group 1) or delayed (Group 2) introduction of TTS (Figure 1), using computer-generated random number function. Group 1 will implement formalised TTS in the first 12 months, with continuation of formalised TTS in the second 12 months. Group 2 hospitals will continue routine trauma care in the first 12 months followed by implementation of formalised TTS in the second 12 months. A statistician not involved with the data collection will be involved to conduct the randomisation. Results of the randomisation will be communicated to the operations manager of the study, who will inform the participating hospitals of the allocation. All patients of individual hospitals will receive the same treatment arm.

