**Table 2 Tab2:** **Data Collection**

***Time***	***Data collection process***
Enrolment	A trained research assistant will prospectively review (electronic) medical records for details on all clinical examinations, pathology tests and diagnostic imaging performed in the first 24 hours of admission. A standardised data collection form will be used for all patients. This review will occur between 24 and 48 hours after initial admission. This data is routinely collected data and as such, patient will not be asked to consent to this.
Enrolment	The patient or proxy will be asked to consent for the follow-up at 1, 6 and 12 months. The patient or proxy will be asked to provide at least two contact numbers and will be informed on the detail of these follow up interviews.
Follow-up	Structured interview at 1, 6 and 12 months after hospital discharge. A list of self-reported missed injuries will be adjudicated by an expert panel to classify the in-hospital missed injury (none, Type I or II) and any Type III injury as definite or likely, as well as to determine clinical significance of any missed injury
Follow-up	A trained research assistant will conduct a scripted follow-up interview that will include questions on delayed diagnosis or missed injuries, level of functioning, time off work and quality of life
	*Study measurements*
	Age
	Sex
	Ethnicity
	Occupation
	ISS score.
	Length of Hospital stay, length of ICU stay
	TTS performance and components of TTS (Additional file 1: Appendix A)
	Diagnoses made after 24 hours in hospital, resultant management (active or conservative), diagnostic procedures or tests.
	Predefined complications of care: post-operative infection (wound infection, cathether-related urinary tract infection, pneumonia, sepsis), and venous thrombo-embolism (Deep Vein Thrombosis, Pulmonary embolism)
	Predefined complications of injury: (ongoing or chronic pain, parasthesia, post-concussion syndrome or symptoms)
	Numbers of CT, MRI and ultrasound scans performed
	Details of unplanned attendances and readmissions to hospital
	Patient quality of life at 1, 6, 12 months (EQ-5D-5 L)
	Proportion of usual days of work or study lost at 1, 6 and 12 months
	Missed injury after hospital discharge
	Medical and nursing time used to assess patients in the first 24 hours
	ICD-10 diagnostic and procedure codes
	Australian-Revised Diagnostic-Related Group (AR-DRG) codes
	Community medical services provided

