### Outcome measures

The primary outcome is Type III missed (Post-hospital discharge) injury rate. This study aims to compare the effect of a formalised TTS compared to routine care on missed injury rates after hospital discharge (type III).

Secondary outcomes are:Maintenance of intervention effect (comparing two 12-month periods in Group 1)*During Hospital Stay*In-hospital missed injury rate (Type I and II combined)Proportion of TTS performedHospital bed days, ICU bed days*During Follow-up (1,6 and 12 months post hospital discharge)*Clinically significant missed injuries (as determined by expert panel)Interventions required for delayed diagnosis (Type I and II) or missed injuries (Type III)Diagnostic imaging usage (CT, MRI, USS)Predefined complications of care and injury (see above)Readmissions to hospitalDays off workQuality of life (EQ-5D-5 L)Days off workMortality

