### Statistical analysis and sample size

The primary analysis will be by intention-to-treat (ITT). Per-protocol analyses will also be performed, based on all patients completing 1, 6 and 12 months follow-up. Based on our prospective study [16], comparing routine care with the formalised TTS group, we anticipate a decrease in post discharge (Type III) injuries from 14% to 9%. We foresee this will be accompanied by an increase of in-hospital injury detection (missed injury Type I and II combined) from 4% to 9%.

The sample size for a cluster-randomized trial requires adjustment of the number of patients that a corresponding individually randomized trial would have needed. This is due to variation between the clusters, and results in a correction using the intra-cluster correlation coefficient (ICC) [21]. Using an alpha of 0.05 and a power of 0.80, a sample size of 638 patients per group, with 1-year follow-up completed, would be required if individually randomised. Our previous study [17] achieved a telephone follow-up rate of 40% at 6 months. Extrapolating a similar conservative follow-up rate at 12 months, a total of 3,190 patients will be required (1,595 for each cohort) to answer the primary hypothesis. To separately answer a before-and-after comparison in Group 2 hospitals a similar sample is required. This results in a sample of 6,380 patients, with complete 1-year follow-up in at least 2,552. Since approximately 0.4% [22] of all ED presentations consist of multi-trauma patients, approximately 1,600,000 ED presentations will be required. For an approximate 24-month recruitment period, this equates to 16 hospitals that have an average annual census of 50,000 presentations. Based on this sample size, the maximum ICC that can be present before the power of the study is reduced below 80% is dependent on cluster size and numbers and presented in Table 3*.*

**Table 3 Tab3:** **Approximate maximum intra-class correlation (ICC) for various cluster sizes and number of intervention hospitals to answer primary hypothesis**

**Number of intervention (and control) hospitals**	**Average size of cluster**	**Maximum ICC to have 80% power to detect 5% difference**
8	400	0.01
15	400	0.02
21	400	0.03
9	300	0.01
15	300	0.02
22	300	0.03
10	200	0.01
16	200	0.02
23	200	0.03

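### Part of the expected rise in in-hospital (Type I and II) injuries could reflect fuller charting, because the form's new-injury list exists only in the TTS phases

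*Protocol article*

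**What the plan says.** Under The intervention, the protocol article describes a TTS form that prompts staff to document history, examination and results, and adds: "The final part of the form includes a (new) injury list". Completing the form within 24 hours of admission is mandatory in TTS phases. The same section gives the target: "the compliance in the intervention hospitals is aimed to be >90%, but will need to be at least 75" (per cent). For the comparator it says: "Standard care is defined as performing a clinical examination based on clinical judgment and without standardised forms".

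Under Randomisation: "Group 2 hospitals will continue routine trauma care in the first 12 months followed by implementation of formalised TTS in the second 12 months". Group 1 uses the form in both years.

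Table 2 gives the source of the in-hospital data: "A trained research assistant will prospectively review (electronic) medical records for details on all clinical examinations", together with pathology and imaging. Under Data collection, newly detected injuries are listed for every patient, and a central blinded panel classes each as Type I, Type II or not new. The research data collection form is the same in both arms.

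The combined Type I and II rate is listed as a secondary outcome. The sample size section anticipates an "increase of in-hospital injury detection (missed injury Type I and II combined) from 4% to 9" (per cent). It also plans a second comparison on this intervention: "To separately answer a before-and-after comparison in Group 2 hospitals a similar sample is required".

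**The concern.** The intervention changes the document from which the outcome is read. In a TTS phase the chart contains a form that asks for new injuries. In standard care the chart contains whatever the team chose to write. The research form is identical, but it can only carry over what is in the chart, and a blinded panel cannot class an injury that nobody recorded.

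The resulting bias runs in the hypothesised direction. If staff found the same injuries in both phases but wrote down more of them with the form, the Type I and II rate would still rise, and the rise would be read as the TTS detecting more. The secondary aim is increased in-hospital detection, and the article intends its results to support making the TTS mandatory or abandoning it. An estimate that mixes detection with documentation weakens that decision. The same contrast is present in the randomised year 1 comparison (Group 1 against Group 2) and in the Group 2 before-and-after comparison.

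**Working it through.** **The plan's own figures.** For 14% against 9%, two-sided alpha 0.05, power 0.80 and no continuity correction, the usual two-proportion formula gives 638 per group, as stated. Then 638 / 0.40 = 1,595 per cohort, 2 × 1,595 = 3,190, and 2 × 3,190 = 6,380. These rest on the Type III rate. The change from 4% to 9% is an assumption of the plan, with no formula behind it to reproduce.

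**Inputs from the article.** The form is absent from Group 2 in year 1. In TTS phases it is available throughout, with planned completion *u* of at least 0.75 and an aim above 0.90. The expected rise is 5 points. There are 1,595 patients per cohort. An average ICC of 0.01 is quoted for blunt trauma.

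**Inputs assumed (not in the article).** True in-hospital detection *T* is the same in both phases, at 6% to 10%. The share of those injuries that reaches the chart is *c* = 0.50 to 0.70 without the form and 0.90 with it.

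**Formula, with no true effect.**
- Standard-care rate = T × c
- TTS-phase rate = T × [0.9u + c(1 − u)]
- Spurious difference = T × u × (0.9 − c)

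| T | c | Standard care | TTS, u = 1.00 | Difference | TTS, u = 0.75 | Difference |
|---|---|---|---|---|---|---|
| 6% | 0.70 | 4.2% | 5.4% | 1.2 points | 5.1% | 0.9 points |
| 8% | 0.60 | 4.8% | 7.2% | 2.4 points | 6.6% | 1.8 points |
| 10% | 0.50 | 5.0% | 9.0% | 4.0 points | 8.0% | 3.0 points |

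As a share of the planned 5 points, that is 24% to 80% at full completion and 18% to 60% at 75% completion.

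**Milder case.** With c = 0.80, the difference is T × u × 0.1. For T = 6% to 10% this is 0.6 to 1.0 points at u = 1.00 and 0.45 to 0.75 points at u = 0.75.

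**What the whole rise would need.** Set T × c = 4% and, with perfect capture on the form, T × [u + (1 − u)c] = 9%.
- u = 1.00: T = 9.0%, c = 4/9 = 44%
- u = 0.75: T = (9 − 0.25 × 4)/0.75 = 10.7%, c = 4/10.7 = 37.5%

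Standard-care records would have to miss 56% to 63% of detected injuries.

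**Chance of a significant result with no true effect.** With 1,595 independent patients per group, the three scenarios give 35%, 82% and 99% at full completion, and 23%, 59% and 93% at 75%. With 1,595 / 8 ≈ 199 patients per hospital and ICC 0.01, the design effect is 1 + 198.4 × 0.01 ≈ 2.98. At the reduced effective sample size the chances are 15%, 38% and 73% at full completion, and 10%, 25% and 51% at 75%. The design effect applies to the parallel-group comparison. Clustering changes how often a false signal appears, not the size of the bias.

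**The case against.** The strongest reply is that a clinician need not label an injury as new. All clinical reviews in the first 24 hours on the ward, pathology, imaging, later diagnoses and resulting management are abstracted in both arms, and the panel decides what is new. An injury is lost only if it appears in none of these sources. This stands in large part: it narrows the gap, especially for injuries seen on imaging, and makes high control capture plausible. It does not close the gap for injuries found on examination, and the article does not restrict Type I and II to imaging-confirmed injuries.

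A reader might infer that charting alone explains the whole move from 4% to 9%, or that the prompt covers every TTS-phase patient. The documents support neither. The first needs standard-care records to miss at least 56% of detected injuries, and no figure in the article suggests that. The second confuses availability of the form with completion, which is planned at 75% or more and follows a 1-month introduction. About 25% of routine-care patients also have a tertiary survey documented without the form.

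A further objection is that the TTS is a physical re-examination, so counting only independently confirmed injuries would remove findings it is meant to make. That is correct, and it is why the confirmed count should stand beside the full Type I and II rate and not replace it. Coded discharge diagnoses may themselves draw on the form, so they are not a clean independent source.

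**Conclusion.** The concern holds in a limited form. Ascertainment of Type I and II injuries differs between phases by design, the bias favours the hypothesis, and neither the identical abstraction form nor the blinded panel removes it. Under the stated assumptions it could contribute about 0.9 to 4.0 of the expected 5 points, and 1 point or less if control records capture 80% or more. These sizes rest wholly on assumed capture rates, because the article gives none. It would go too far to say that the secondary result could not be interpreted. The supportable statement is that an observed rise may be partly inflated by documentation. The outcome affected is secondary, and the sample size, which rests on the Type III rate, is unchanged.

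**What to change.** Keep the timing-based Type I and II definition, and add the following:

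1. The abstractor flags, for each newly detected injury in every phase, the source or sources in which it appears (TTS form, ward note, imaging report, operation note).
2. Pre-specify a parallel between-phase comparison restricted to injuries confirmed in a dated imaging report or operation note and absent from the injury list at the end of the ED primary and secondary survey. Apply it to both the year 1 and the Group 2 before-and-after comparisons.
3. Report injuries recorded only on the TTS form as a separate line.
4. Claim increased in-hospital detection only if the confirmed-injury comparison agrees with the full Type I and II comparison.

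The cost is small: a source field in the abstraction, one extra pre-specified analysis, and a check that operation notes are among the records read. The downside is that the confirmed-only rate is lower in both phases and omits injuries diagnosed only on examination. It is therefore conservative and should be read beside the full rate.

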	Primary resource use through Medicare Benefit Scheme (MBS) and the Pharmaceutical Benefit Scheme (PBS) for a 12-month period following the index hospitalizations

If not contactable during initial phone call, up to five attempts will be made. Patients can indicate during follow-up that an injury was missed during their hospital stay. These self-reported injuries will be checked against relevant medical records and imaging reports and defined by the expert panel as missed injury (definitely, likely, unlikely, unknown) or a complication of care or injury. An injury will only be classified as definite or likely (Type III) ‘missed injury’ if there is no evidence (in medical record or radiology report) of the self-reported injury during the hospital stay. The panel will determine the clinical significance of these injuries based on change in management and expected effect on (duration) of morbidity.

Patients who reported a missed injury will be offered appropriate pathways for follow-up. Finally, we will undertake a search of the Death Registry to identify the mortality rate at 12 months post hospital discharge and cause of death.

Appropriate data on the associated cost-implications will be collected during the trial in order to conduct a cost-effectiveness analysis. Items identified that require appropriate measurement and valuation include: medical and nursing time used to assess patients in the first 24 hours, requested advanced imaging type and frequency, ICU length of stay, hospital length of stay, ICD-10 diagnostic and procedure codes, Australian-Revised Diagnostic-Related Group (AR-DRG) codes, patient time-off work, community medical services provided, and re-admissions to hospital.

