### Blinding and choice of outcomes

Blinding the treating staff to the intervention is challenging, but the patient will be blinded since all patients will be receiving a standard care variation (routine versus routine plus formalised TTS) and will not be informed of the specific intervention. However, relatively objective endpoints will be adjudicated by a blinded expert panel and a prospective randomised open-label, blinded end-point (PROBE) methodology can be used [24] and has the advantage that procedures resemble real-world practice and are thus more likely to be broadly generalisable [25,26].

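### A performed TTS is defined by a form in intervention phases and by a chart note in standard care, so the uptake comparison is not like-for-like

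*Protocol article*

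**What the plan says.** The section The intervention defines the event by condition. For the intervention phases: "A TTS in the intervention phases is defined as completion of the formal TTS form within 24 hours of admission". For the comparison: "where during standard care it is defined as a documented tertiary survey as part of a clinical examination within 24 hours of admission". The same section says of the control condition: "Standard care is defined as performing a clinical examination based on clinical judgment and without standardised forms". The form therefore exists only in intervention phases, where staff are directed to "mandatory TTS form completion as part of routine care within 24 hours of admission". One further sentence, not limited to either condition, rules out counting a mere review of injuries already known.

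The Outcome measures section lists the share of patients with a TTS among the secondary outcomes. The Abstract says 20 to 25% of trauma patients now have a TTS and expects at least 75%. The section The intervention gives about 25% for routine care, and a compliance aim above 90% with a minimum of 75% in the intervention hospitals. The Data collection section says that the record will show both whether a TTS was documented and which of its components were done, with the same processes in both Groups.

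**The concern.** One outcome name covers two measurements. In an intervention phase the count depends on whether a piece of paper was completed. In standard care it depends on whether an abstractor finds a tertiary survey in the notes. A difference between the two rates mixes a change in what clinicians do with a change in what is counted. This affects the between-arm comparison in the first 12 months and the before-and-after comparison in Group 2, where the definition changes when the intervention starts.

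The uptake contrast matters for interpretation. The Background suggests that the earlier before-and-after study may have found no difference in missed injuries because uptake rose only from 27% to 42%, that is by 42 − 27 = 15 points. The present trial is meant to improve on that. If missed injuries again do not differ, readers will look at the uptake contrast to decide whether the TTS failed or was never delivered. They can do so only if both rates measure the same thing.

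**Working it through.** **1. What the point does not touch.** The plan's 638 per group reproduces from 14% v 9%, two-sided alpha 0.05 and power 0.80:

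n = [1.960 × √(2 × 0.115 × 0.885) + 0.8416 × √(0.14 × 0.86 + 0.09 × 0.91)]² / 0.05² = (0.8843 + 0.3785)² / 0.0025 = 637.9, rounded up to 638.

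No uptake rate enters this calculation.

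**2. The two definitions applied to the same events.**

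| Event within 24 hours of admission | Standard care | Intervention phase |
|---|---|---|
| Full re-examination and review of results, written in the notes, no form | Counts | Does not count |
| Form completed, re-examination only partial | Cannot occur; an equivalent note counts only if judged a tertiary survey | Counts |
| Review of known injuries only | Excluded | Excluded |

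The last row agrees across conditions; the first two do not. The first lowers the intervention rate relative to standard care, and the second can raise it.

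**3. Size, on assumed values.** The planned contrast is 75 − 25 = 50 points, or 75 − 20 = 55 points from the lower baseline. The documents give no error rates, so each error is varied alone over a range. *True* here means the rate under one common component standard.

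- Standard care under-counts, capturing a share s of true surveys: true rate = recorded / s. From 25%: s = 1, 0.8, 0.5 gives 25%, 31.3%, 50%, and a gap to 75% of 50, 43.8, 25 points. From 20%: 20%, 25%, 40%, and gaps of 55, 50, 35 points.
- Standard care over-counts, with only a share w of counted notes meeting the standard: true rate = 25% × w. w = 1 to 0.5 gives 25% to 12.5%, and a gap of 50 to 62.5 points.
- Intervention over-counts, with only a share v of completed forms meeting the standard: true rate = 75% × v. v = 1 to 0.5 gives 75% to 37.5%, and a gap to 25% of 50 to 12.5 points.
- Intervention under-counts, with u points of patients fully surveyed in the notes without a form: true rate = 75% + u. u can run from 0 to 25 points (all patients without a form), giving 75% to 100% and a gap of 50 to 75 points.

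Two of the four errors shrink the contrast and two enlarge it. Nothing in the documents says which dominates.

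**The case against.** The case for the plan is reasonable. The form is part of the intervention, so completing it is the natural measure of fidelity. The 75% minimum is set for compliance in the intervention hospitals, not as a between-arm test. Both definitions require documentation in the same 24-hour window and share the same exclusion. Component data are to be collected by the same procedures in both arms, so a common measure could be derived later. Uptake is one secondary process measure, and the error has no established direction.

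Most of that stands, and it limits the point. It does not remove it. The TTS rate is listed as an outcome, the Abstract treats it as one quantity rising from 20 to 25% to at least 75%, and the definition given for it changes with the condition. Data that could support a common measure are not yet that measure.

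Three stronger readings are tempting, and the documents do not support them.

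- *The primary adjudication is not blind, because the panel sees the form.* The text says: "These self-reported injuries will be checked against relevant medical records and imaging reports and defined by the expert panel as missed injury". It does not say that the panel opens unmasked notes or that the form reaches it. The Abstract, Aims and hypotheses, Data collection, and Blinding and choice of outcomes all describe a blinded panel, the last in the words "relatively objective endpoints will be adjudicated by a blinded expert panel". How the material is masked is detail that an article may leave to the full protocol.
- *The form biases the primary outcome towards TTS by supplying evidence in one arm.* A Type III injury counts only "if there is no evidence (in medical record or radiology report) of the self-reported injury during the hospital stay". An injury entered on the form was detected in hospital, and moving detection into the hospital stay is the hypothesis under test. Control notes and radiology reports serve as evidence in the same way.
- *The Type I and II wording, which refers to the TTS, distorts the in-hospital outcome.* That outcome is Types I and II combined, and Table 1 already gives a 24-hour boundary between them.

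**Conclusion.** The point holds for uptake only. Followed as written, the secondary outcome and the 20 to 25% v 75% contrast are partly a comparison of definitions. The size cannot be estimated from the documents, and the direction is unknown; the figures above are illustrations on assumed error rates, taken one at a time. The 75% figure remains sound as a compliance benchmark within intervention hospitals. The sample size is not affected, and the documents give no ground for extending the point to the primary outcome or its adjudication. The practical consequence is that a reported rise in TTS performance could not be read cleanly as a change in practice, which weakens the explanation of either a positive or a null primary result.

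**What to change.** For the between-arm and before-and-after comparisons, count a TTS as performed, in all hospitals and periods, when the same prespecified components are documented within 24 hours of admission: re-examination of the body regions plus review of imaging and pathology. Derive this from the component data already to be collected in both groups, and keep the exclusion of reviews of known injuries only. Report form completion separately, in intervention phases, as fidelity against the 75% benchmark.

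Two practical points. The appendices are not shown, so the sponsor should confirm that the collection tool records each component for every patient, and not only where a TTS has already been judged present. The measure would still be of documented performance: because the form prompts documentation, some difference in recording between conditions may remain and should be acknowledged when the result is reported.

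The cost is a revised definition, some extra coding by the research staff, and possibly a smaller uptake contrast than the form-based count would show. Recruitment had not begun when the article was written, so the change can be made before any data are collected.
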